| Dropout/Removal Criteria | - 1. Participants who do not meet the screening criteria;   2. Participants who are unable to evaluate for efficacy or unable to evaluate safety without receiving 1 dose of the drug;   3. Participants who are treated with chemotherapy, surgical or experimental drugs other than this protocol during the trial;   4. Participant's concurrent use of China Food and Drug Administration (CFDA)-approved modern herbal agents and immunomodulatory agents for the treatment of tumors;   5. Participants who do not follow the dose, method, and course of treatment according to the study protocol. |
| Termination Criteria | Subject must termination the study if the following cases occur (including but certainly not limited to):   - 1. Disease progression (PD) determined according to RECIST 1.1 criteria or considered clinically progressive.   2. Termination of treatment decided by the investigator from the patient's best interests.   3. Occurrence of intolerable adverse reactions or severe adverse events confirmed by the investigator.   4. Patients with poor compliance, using drug amounts outside the range of 80% to 120% of the prescribed dose.   5. Patient withdrawal of informed consent.   6. Initiation of other anti-tumor drug treatments affecting efficacy judgment (such as chemotherapy, targeted therapy, or biologic agents).   7. Unexpected pregnancy. |
| Study Schedule | Estimated date of the start of the study: August 2019  Estimated enrollment date of the last subject: August 2020  Estimated date of the end of the study: August 2021 |
| Study Procedures | TQB2450 plus anlotinib hydrochloride capsules were administered in a 21-day cycle until disease progression or intolerance. |
| Primary effect endpoints | Duration of response (DoR); overall survival (OS); 12-month progression-free survival rate; disease control rate (DCR); objective response rate (ORR) (assessed per RECIST version 1.1 at the following time points: 3 weeks after the first therapy, then every 6 weeks thereafter during therapy.) |
| Primary safety endpoints | Dose-limiting toxicities (DLT); maximum tolerable dose (MTD); vital signs; laboratory index; adverse event (AE); immune-related adverse event (irAE); serious adverse event (SAE) according to NCI CTCAE version 5.0. |

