**(2) AEs**

AE is defined as any untoward medical occurrence in a subject who received study drugs, but which does not necessarily have to have a causality to treatment.

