**(5) Causality assessment of AEs to drugs**

In this study, the relationship of AEs to TQB2450, anlotinib, and immune response will be assessed.

AEs was categorized as definitely-related, probably-related, possibly-related, possibly-unrelated, and definitely-unrelated.

Investigator(s) are required to assess the causality of AEs to study drugs, according to the following 5 criteria.

(1) Whether the administration time and the suspected AEs exhibit a reasonable relationship;

(2) Whether the suspected AEs fulfill the criteria for the typical reactions of the drug;

(3) Whether the suspected AEs can be explained by the effects of the combined drug, patient’s clinical condition, or other therapies;

(4) Whether the suspected AEs disappear or are mitigated after drug discontinuation;

(5) Whether the same AEs recurred after repetitive administration of the study drugs.

AEs will be calculated as the sum of definitely-related, probably-related, and possibly-related events.

|  | 1 | 2 | 3 | 4 | 5 |
| --- | --- | --- | --- | --- | --- |
| Definite | + | + | - | + | + |
| Probable | + | + | - | + | ? |
| Possible | + | + | ± | ± | ? |
| Unlikely | + | - | ± | ± | ? |
| Unrelated | - | - | + | - | - |

Note: +, Yes; -, No; ±, probably Yes or No; ?, unknown.

- - 1. Serious AEs (SAEs)

SAE is defined as any adverse event that results in any one of the following unanticipated events during the clinical trial period:

- 1. Death and life-threatening events
  2. Events leading to in-patient hospitalization or prolongation of existing hospitalization;
  3. Events causing persistent or severe disability;
  4. Events causing incapacity
  5. Events causing congenital anomalies/birth defects;

Events that should be not classified as SAEs:

1. Hospitalization due to the use of study drugs.
2. Hospitalization due to protocol-specified procedures (e.g., pathological tissue sampling); however, the event leading to in-patient hospitalization or prolongation of existing hospitalization due to these procedures should be classified as SAE;
3. Hospitalization for planned treatment of the disease。

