Male subjects were informed by the informed consent that if their partner pregnant during the study period or within 6 months after the last dose of study drug, they should immediately notify the investigator. Investigator(s) are required to complete the Clinical Trial Pregnancy Report Form and report to the sponsor or their designated personnel within 24 hours of being informed of a pregnancy occurrence and submit it to the sponsor or their designated personnel. Investigator should provide advices, and discuss the risks of continuing the pregnancy and potential impacts on the fetus, meanwhile, discuss with her primary physician and/or obstetrician to discuss reasonable solutions. If subjects decide to continue the pregnancy, the investigator should collect detailed information about the course and outcome of the pregnancy in detail. Meanwhile, partners with pregnancy needs to sign an authorization form, allowing the use and disclosure of the health information related to this pregnancy and agreeing to undergo subsequent follow-ups for the pregnancy. After signing authorization, investigator is required to submit the Clinical Trial Pregnancy Report Form when obtaining the latest information on the pregnancy process and outcomes.

(3) Spontaneous abortion

Spontaneous abortion should be reported as SAEs (abortion has great significant significance assessed by sponsor) and recorded in the eCRF. Investigator(s) is required to report the SAE after aware of the occurrence of spontaneous abortion, as per the procedure in 6.4.3 section.

(4) Congenital anomalies/birth defects

Any congenital anomalies/birth defects in infants born to female subjects or female partners of male subjects who had taken study drugs should be reported as SAEs in the eCRF. Investigator(s) is required to report the SAE after aware of the occurrence of congenital malformations/birth defects, as per the procedure in 6.4.3 section.

- - 1. Management of common AEs

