**6.5.6.1 Common AEs related to TQB2450**

Types and treatment recommendations of immune-related adverse events (irAEs) caused by TQB2450 are listed in Appendix 6.

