**(2)** **Hypertension**

In previous studies, anlotinib is associated with the frequent occurrence of hypertension and the incidence of grade 3 or higher hypertension was 13.61%. During this study, subjects are recommended to monitor blood pressure during treatment. In the event of a hypertensive event, the following managements are recommended:

Grade 1: Pre-hypertension (systolic blood pressure [SBP] 120-139 mmHg or diastolic blood pressure [DBP] 80-89 mmHg); No indication for antihypertensive drugs and blood pressure is monitored.

Grade 2: Stage 1 hypertension (SBP 140-159 mmHg or DBP 90-99g mmHg); Medical intervention is required. For recurrent or persistent (≥24 hours), symptomatic hypertension with >20mmHg SBP increases or >140/90 mmHg increase of previously normal range, monotherapy and blood pressure monitoring are required. Thiazide diuretic, angiotensin-converting enzyme inhibitors (ACEI), angiotensin II receptor blockers (ARB), beta-blocker, or calcium-channel blocker are commonly used.

Grade 3: Stage 2 hypertension (SBP ≥160 mmHg or DBP ≥100 mmHg); Medical intervention is required. Multidrug therapy is required, commonly using a thiazide diuretic combined with an ACEI, beta-blocker, or calcium-channel blocker.

Grade 4: Life-threatening (e.g., malignant hypertension, persistent neurological deficit, hypertensive crisis). Urgent treatments are required.

Hypertension emergencies: SBP >120 mmHg accompanied by acute or progressive target organ damage (e.g., Cerebral infarction, intracranial or subarachnoid hemorrhage, hypertensive encephalopathy, etc.); among them, the progressive or rapidly progressive hypertension based on chronic essential hypertension is the most common (about 40%-50%).

Hypertension urgencies: SBP >120 mmHg with no or minor organ damage.

In case of hypertensive crisis, subjects should discontinue the study treatment and withdraw from the study.

When subjects occur elevated blood pressure during vital sign measurements, a second measurement should be taken after a 15-minute rest. If the elevation is repeated and reaches the grade 2, it can be defined as an AE of hypertension. If the time of improvement from the first occurrence of hypertension to its reappearance is less than 1 week, it is identified as one AE and record the highest level of severity. The start time is defined as the time of the first hypertensive episode, and the end time is defined as the last outcome time of hypertension.

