**8.2.5 Safety analyses**

Safety analysis includes AEs/adverse reactions, serious AEs/adverse reactions, laboratory tests, vital signs, physical examination, ECOG score, 12-lead electrocardiogram.

- - - 1. **AEs**

Medical coding of adverse events/adverse reactions/immune-related adverse events was performed with the use of MedDRA 21.0. The occurrence of adverse events/adverse reactions/immune-related adverse events, serious adverse events/adverse reactions/immune-related adverse events, adverse events/adverse reactions/immune-related adverse events leading to withdrawal, and adverse events/adverse reactions/immune-related adverse events leading to death were summarized, the number and times of occurrence were listed, and the incidence was calculated. The incidence of adverse events/adverse reactions/immune-related adverse events and serious adverse events/adverse reactions were summarized according to system organ classification (SOC) and preferred terminology (PT), and the number and incidence of adverse events/adverse reactions were listed. The association and toxicity grade of AEs/AEs (NCI CTCAE v5.0) were summarized according to SOC and PT, and the number and incidence of AEs/AEs were listed. The list describes the details of the occurrence of each adverse event/adverse reaction for each subject.

- - - 1. **Laboratory tests**

The laboratory tests were classified according to clinical significance, namely normal, abnormal without clinical significance, abnormal with clinical significance or normal and abnormal. The laboratory tests were summarized descriptively by frequency and percentage using cross-classification table.

Lists describe occurrences of normal before treatment but abnormal after treatment, as well as subjects who were abnormal before treatment but worsened after treatment. The mean, standard deviation, median, quartile, minimum and maximum values of routine blood test, blood biochemistry, four coagulation tests, thyroid function, lipase and amylase were listed. The measured values and changes before and after treatment were described. Paired *t* tests were performed when necessary.

Describe the proportion of subjects with abnormal changes who have “abnormal clinical significance”, in which the investigator judges whether the abnormality has clinical significance.

| Type | Tests |
| --- | --- |
| Hemanalysis | WBC, ANC, LYM, RBC, Hb, PLT |

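### The SAE definition admits only unanticipated outcomes, which mixes expectedness into seriousness and leaves the SAE endpoint open to literal under-counting or to differences between sites

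*Protocol*

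**What the plan says.** The general definition in Protocol section 6.5, Serious AEs (SAEs), reads: "SAE is defined as any adverse event that results in any one of the following unanticipated events during the clinical trial period". The outcomes listed beneath it are death and life-threatening events, new or prolonged in-patient stays, disability, incapacity and birth defects. A short list of hospitalizations that do not count follows, the first being "Hospitalization due to the use of study drugs".

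The AE definition earlier in section 6.5 carries no expectedness condition: "AE is defined as any untoward medical occurrence in a subject who received study drugs". For congenital anomalies and birth defects, the later text on pregnancy outcomes says without qualification that they "should be reported as SAEs in the eCRF".

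The Synopsis lists "serious adverse event (SAE) according to NCI CTCAE version 5.0" among the primary safety endpoints. Section 8.2.5 plans to summarise and calculate the incidence of "serious adverse events/adverse reactions/immune-related adverse events". No other general SAE definition appears in the available text.

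**The concern.** Seriousness and expectedness answer different questions. Seriousness asks what the event led to. Expectedness asks whether it could have been foreseen. Making the listed outcomes conditional on being unanticipated puts the second question inside the first.

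The condition has something to act on here, because both drugs come with toxicities that the protocol names in advance, some with serious outcomes already described. An investigator who follows the words strictly has grounds not to classify such an outcome as an SAE. Another who takes the word as loose drafting will classify it. The SAE rate of the combination, a primary safety endpoint, would then depend partly on how each site reads one adjective.

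**Working it through.** The point concerns the wording of a definition, and the plan gives no figure to reproduce. The check sets the definition beside every other place that bears on it.

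**1. Does the protocol foresee serious outcomes, and not only toxicities?** It does.
- Table 5.5-1 describes grade 3 infusion reactions with admission to hospital and grade 4 reactions as life-threatening.
- Section 6.5.6.2 (2) describes grade 4 hypertension as life-threatening and covers hypertensive crisis.
- Table 5.5-10 lists immune reactions up to grade 4, including encephalitis, Guillain-Barre syndrome and myasthenia gravis. Section 6.5.6.1 adds: "Types and treatment recommendations of immune-related adverse events (irAEs) caused by TQB2450 are listed in Appendix 6".
- The text after Table 5.5-10 names sepsis, herpes encephalitis and retroperitoneal hemorrhage as risks seen with similar drugs.
- Section 6.5.6.2 (6) foresees gastrointestinal bleeding that needs transfusion or a surgeon.

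**2. Does any other text remove the condition?** Not in general. The AE definition has no such condition but does not define seriousness. The pregnancy text drops it for birth defects, and calls spontaneous abortion an SAE with no expectedness test. Birth defects are therefore restricted to unanticipated cases in one place and included without restriction in another.

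**3. What uses the definition?** The SAE endpoint in the Synopsis and the SAE incidence summaries in section 8.2.5. Neither brings a definition of its own.

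**4. What is protected regardless?** Section 6.5, under observation and recording of AEs, captures events whatever their causality, with severity, outcome and management. Section 8.2.5 tabulates toxicity grade by system organ class and preferred term, and separately summarises events leading to withdrawal and to death. The SAE classification is what is at risk, not the record of the event.

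**5. Can the size be computed?** No. The only relevant rate is for severity: section 6.5.6.2 (2) says that in previous studies "the incidence of grade 3 or higher hypertension was 13.61" per cent. Applied to the 54 planned phase II patients:
- expected patients = 54 × 0.1361 = 7.35;
- P(at least one) = 1 − (1 − 0.1361)^54 = 1 − 0.8639^54 ≈ 0.9996.

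Grade 3 is defined there by blood pressure (systolic ≥160 or diastolic ≥100 mmHg), not by admission or death, so 7.35 is not a count of SAEs. Assuming the previous rate carries over, the calculation shows only that severe toxicity of an anticipated kind is close to certain to occur. The share that becomes serious is not given.

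**The case against.** The strongest reply is grammatical. The adjective attaches to the resulting outcome, not to the toxicity behind it. An unplanned admission for a well-known toxicity is still an unanticipated admission. The exclusion list partly supports this: two of its three items concern admissions for protocol procedures or planned treatment, and the procedures item says that an event which causes or prolongs a stay because of such a procedure does count. That points to planned versus unplanned rather than expected versus unexpected. The word may also be a slip for *untoward*, as used in the AE definition.

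Much of this stands. A reader might infer that every serious event from a listed toxicity is excluded, so that the drugs' main known harms vanish from the SAE tables. The documents do not support that. Section 8.2.5 plans a summary of serious immune-related events, while Table 5.5-10 ends with a row for all other immune-related events. If listed reactions could never be serious, that summary would always be empty. The protocol evidently means to count them.

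A reader might also infer that such events escape expedited reporting. That cannot be confirmed. The pregnancy text refers to an SAE procedure in section 6.4.3, but no such procedure appears in the available text.

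The reply does not remove the defect. The protocol foresees admission and threat to life as outcomes of infusion reactions, and threat to life from hypertension. Even with the adjective tied to the outcome, those can be called anticipated. A probable slip explains the wording, but sites classify from the text as it stands.

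**Conclusion.** The definition is wrong as written, in a limited way. It makes seriousness partly depend on expectedness. Followed literally, it can leave out serious outcomes that the protocol describes in advance; followed loosely, it lets sites differ. It also disagrees with the protocol's own rule for birth defects. The SAE primary safety endpoint and the SAE incidence tables in section 8.2.5 are affected; the recording and grading of AEs and the tables of events leading to death or withdrawal are not.

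The number of SAEs affected is unknown, and 7.35 must not be used as that number. The conclusion assumes that no general SAE definition or overriding rule stands in the text that is not available. The exclusion of hospitalizations tied to study drug use is a separate question: settling it would still leave deaths, life-threatening events and disability under the same condition.

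**What to change.** Delete *unanticipated* from the SAE definition in section 6.5 and from any SAE form that repeats it, so that seriousness rests on the listed outcomes alone. If expectedness is wanted for reporting, record it as a separate field. The definition then agrees with the rule for birth defects.

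The cost is one word in the protocol, a matching check of the form, and possibly a higher SAE count. No dose, treatment rule, sample size or efficacy analysis changes. If SAEs have already been classified under the present wording, the recorded AEs can be reviewed against the listed outcomes before database lock.

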**Protocol Synopsis**

| Protocol Title | TQB2450 plus anlotinib in EGFR+ advanced non-small-cell lung cancer patients failed to prior EGFR TKI therapies: a multi-center, single-arm, phase I/II study |
| --- | --- |
| Protocol Number | ALTER-L038 |
| Sponsor | Jiangsu Cancer Hospital |
| Co-sponsor | Chia-tai Tianqing Pharmaceutical Co., Ltd. |
| Study Nature | A phase I/II study |
| Study Population | Patients with EGFR+ advanced non-small-cell lung cancer who failed prior EGFR TKI therapies |
| Objective | Phase I part: To determine the maximum tolerable dose (MTD) of anlotinib and TQB2450.  Phase II part: To evaluate the efficacy and safety in EGFR+ advanced non-small-cell lung cancer patients who failed prior EGFR TKI therapies |
| Study Design | Phase I part: 3+3 dose-escalation study  Patients are treated with anlotinib at 3 levels of 8 mg, 10 mg, and 12mg, and TQB2450 at a fixed dose of 1200 mg. The dose-escalation starts with the combination of 8mg anlotinib and TQB2450. Monitor dose-limiting toxicity (DLT) during one cycle to determine the MTD for patients. MTD is defined as the maximum dose with ≤33% risk of DLT. DLT is defined as drug-related toxicity occurring during the first 21 days of therapy that results in grade 4 hematological toxicity, neutropenia (ANC<1000/μL, fever of ≥38.5℃), grade 2 hepatic or renal dysfunction (lasting >7 days despite symptomatic treatment), and grade 3 or higher non-hematological toxicity (excluding alopecia).  Phase II part: A multi-center, single-arm, phase II study  The eligible patients are treated with anlotinib at the dose of 12 mg plus TQB2450 at the dose of 1200 mg, which is determined in phase I study. All patients were treated until events meeting the termination criteria. The efficacy and safety of anlotinib combined with TQB2450 are further evaluated. |
| Planned Sample Size | Phase I part: 3-18 patients  Phase II part: 54 patients |
| Principal Investigator | [name] |
| Clinical Study Unit | Jiangsu Cancer Hospital |

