**(3) Observation and recording of AEs**

Any medical events that occurred from starting treatment until 28 days after the end of the study drug or the initiation of other anti-tumor therapy, regardless of its causality to study drugs, are considered to be an AE.

If laboratory abnormalities were part of a syndrome, the syndrome or diagnostic finding (e.g., anemia) rather than the laboratory finding (i.e., decreased hemoglobin) will be recorded.

The following information about AEs should be recorded, including time of AE occurrence (starting time) and recovery time (ending time), severity, the causality of AEs to study drugs, follow-up, outcomes, and managements.

AEs are followed-up until the disease is stable, normalized, and returned to baseline.

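### As written, section 6.5 exempts some drug-toxicity admissions from SAE status, and its causality table can never score an event that is not typical of the drug as related

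*Protocol*

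**What the plan says.** **SAE definition (Protocol, section 6.5, Serious AEs).** One of the seriousness criteria is "Events leading to in-patient hospitalization or prolongation of existing hospitalization". A second list follows under "Events that should be not classified as SAEs". Its first item is "Hospitalization due to the use of study drugs", with nothing added. Its second item, on admissions for protocol procedures, has a qualification: "however, the event leading to in-patient hospitalization or prolongation of existing hospitalization due to these procedures should be classified as SAE". Its third item covers admission for planned treatment of the disease.

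**Causality (Protocol, section 6.5, Causality assessment of AEs to drugs).** Five questions are answered for each event. The second is "Whether the suspected AEs fulfill the criteria for the typical reactions of the drug". A table turns the answers into Definite, Probable, Possible, Unlikely or Unrelated. The section then says "AEs will be calculated as the sum of definitely-related, probably-related, and possibly-related events".

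**AE definition (Protocol, section 6.5, Observation and recording of AEs).** Medical events in the observation window, "regardless of its causality to study drugs, are considered to be an AE".

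**Where the classifications are used.** Section 8.2.5 tabulates AEs, adverse reactions, SAEs and serious adverse reactions by system organ class and preferred term. The synopsis also brings causality into dose-limiting toxicity: "DLT is defined as drug-related toxicity occurring during the first 21 days of therapy".

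**The concern.** The first exclusion item can be read as exempting an admission caused by the drug, which contradicts the hospitalization criterion a few lines above it. The protocol saw the need for a qualification where procedures cause harm, but gave none where the study drug does.

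The causality table makes being typical of the drug a condition for every related category. This suits the trial poorly. Section 1.2.4.1 reports 34 subjects enrolled in the TQB2450 phase I study, so what is typical of that drug is not yet well known, and the phase I part here studies a new combination. A toxicity that belongs to the combination and to neither drug alone is the kind of signal that the table cannot label as related.

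At stake is whether the SAE and adverse-reaction tables show drug-caused harm as such.

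**Working it through.** No planned figure is involved, so the check compares passages and enumerates the table.

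**1. SAE lists side by side**

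| Cause of admission | Listed as not an SAE | Resulting event returned to SAE status |
| --- | --- | --- |
| Use of study drug | Yes | No clause |
| Protocol procedure | Yes | Yes, explicitly |
| Planned treatment of the disease | Yes | No clause |

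The exclusion concerns hospitalization only. An event that is also fatal, life-threatening, disabling, incapacitating or a congenital anomaly still meets another criterion. The literal effect is therefore confined to events that are serious through hospitalization alone.

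**2. Causality table as printed** (criteria: 1 timing, 2 typical reaction, 3 other explanation, 4 improves on stopping, 5 recurs on repeat dosing)

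| Category | 1 | 2 | 3 | 4 | 5 |
| --- | --- | --- | --- | --- | --- |
| Definite | + | + | - | + | + |
| Probable | + | + | - | + | ? |
| Possible | + | + | ± | ± | ? |
| Unlikely | + | - | ± | ± | ? |
| Unrelated | - | - | + | - | - |

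Every row above Unlikely has + on criterion 2. Possible and Unlikely differ in that cell alone.

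**3. Enumeration with criterion 2 = No.** Criteria 1, 3 and 4 can each be Yes or No, and criterion 5 can be Yes, No or unknown. That gives 2 × 2 × 2 × 3 = 24 patterns. The sign ± is read as Yes or No. The sign ? is read strictly (unknown only) and widely (any answer).

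| Patterns with criterion 2 = No | Strict ? | Wide ? |
| --- | --- | --- |
| Criterion 1 = Yes (12) | 4 Unlikely, 8 fit no row | 12 Unlikely |
| Criterion 1 = No (12) | 1 Unrelated, 11 fit no row | 1 Unrelated, 11 fit no row |
| Reaching Definite, Probable or Possible (of 24) | 0 | 0 |

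The case (+, -, -, +, ?), meaning fitting timing, atypical, no other explanation, improves on stopping and recurrence unknown, is Unlikely under both readings. If it also recurs on repeat dosing (+, -, -, +, +), it is Unlikely under the wide reading and fits no row under the strict one.

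**4. Counting.** Only Definite, Probable and Possible are summed, so the cases in step 3 are left out of the related total. The protocol calls that total AEs, while its own AE definition disregards causality. Both cannot hold. Section 8.2.5 lists AEs and adverse reactions separately, which suggests that adverse reactions were meant.

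**The case against.** The first exclusion item may simply mean admission to receive the drug. Its two neighbours describe planned admissions, and TQB2450 is infused at every cycle (section 5.5). Section 8.2.5 plans tables of serious adverse reactions, so drug-caused serious events are evidently meant to be captured. That intention is likely. But the words used normally mean caused by, and a multicentre protocol should not leave sites to choose between the readings.

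On causality, the word typical is not defined as already listed, and relationship to immune response is assessed alongside the two drugs. A generous assessor could answer Yes to criterion 2 more often. That makes atypical events fewer but does not change what the table does with them.

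Several stronger readings are tempting, and the protocol does not support them:

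- **That such events drop out of expedited reporting.** The SAE reporting procedure is not in the text available for this review, so this cannot be checked. The causality table does not affect SAE status either, since the SAE definition has no causality condition.
- **That every drug-toxicity admission is exempt.** Events meeting another seriousness criterion remain SAEs.
- **That any atypical event becomes Unlikely.** This holds only when timing is plausible. Otherwise the event is Unrelated or fits no row.
- **That atypical events disappear from the safety data.** They are still recorded, graded and tabulated as AEs. What is lost is the related label.
- **That dose escalation is pushed upward.** Section 6.3 lists dose-limiting toxicities without a causality condition, and nothing routes those decisions through the causality table. An effect arises only under the synopsis wording.

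**Conclusion.** Both rules misclassify events if followed as written. The exemption can remove SAE status from drug-caused admissions that are serious through hospitalization alone. This rests on the literal reading, which the wording permits and nothing in the list rules out. The causality result needs no such assumption about intent: 0 of 24 patterns with criterion 2 = No reach a related category under either reading of the unknown sign. Such events are missing from the adverse-reaction counts but not from the AE record.

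The protocol gives no expected number of drug-toxicity admissions or atypical events, so the size of the undercount cannot be stated. Any effect on dose-limiting toxicity is conditional on the synopsis definition, which differs from section 6.3 on causality; the two must be reconciled. The point deserves correction because the errors run toward understating drug-caused harm and take only a few lines to remove.

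**What to change.** 1. Replace the first exclusion item with wording such as *Hospitalization solely for administration of study drug, without an adverse event*. Add that an adverse event caused by study drug that leads to or prolongs hospitalization is an SAE.
2. In the causality table, let an event with criterion 1 = +, criterion 2 = - and criterion 3 = - be scored Possible. When criterion 2 is -, require criterion 3 = + for Unlikely. Merely changing criterion 2 to ± in the Possible row would not do: (+, ±, ±, ±, ?) contains every Unlikely pattern, so the two rows would no longer be distinct.
3. State whether ? means unknown only or any answer. With change 2 and the wide reading, the 12 patterns with fitting timing and an atypical event split into 6 Possible (criterion 3 = -: 2 × 3) and 6 Unlikely (criterion 3 = +: 2 × 3), without overlap. Under the strict reading the split is 2 and 2, and 8 still fit no row.
4. Change the counting sentence so that the sum of the three related categories is called adverse reactions, in line with the AE definition.
5. Reconcile the synopsis and section 6.3 on whether a dose-limiting toxicity must be drug-related.

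The cost is a few lines of protocol text and a note in the eCRF guideline. In use, expect somewhat more SAE reports and more events scored as possibly related.
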